### Research questions

We wanted to know whether, and to what extent, the content of the information brochure distributed nationwide in Germany influences women’s intention to participate in mammography screening, and whether EBPI-relevant, transparent information regarding the potential benefits and harms of early detection screening influences this intention. In detail, our research questions are:

1. What influence does an information brochure including relevant facts and figures on the harms and benefits of mammography screening ('new brochure’) have on women’s intention to take part in screening, compared to a brochure that mainly promotes the screening while omitting relevant information ('old brochure’)?

2. Do different information brochures lead to different knowledge about the potential benefits and harms of mammography screening?

3. Are there any other factors (beside the contents of brochures) influencing the decision to take part (for example, personal experience with breast cancer, marital status)?

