## Methods

This is a controlled two-armed single-blind questionnaire study. Women will be randomized into two groups: group A will receive the 'new brochure’ (Additional file 1) with facts and figures corresponding to current evidence on outcome. Group B will receive the 'old brochure’ (Additional file 2) with little, merely promoting, information.

We are addressing women aged 48 to 49 yrs, that is, one or two years before eligibility for mammography screening. For ethical reasons we did not choose the eligible age, so as not to influence the immediate decision of the women regarding participation in screening. Also, women aged 50+ are more likely to have received and studied the 'new brochure’ already, so the study’s control arm receiving the 'old brochure’ would probably have been contaminated. The women are recruited via their GPs, whom we contact with a request to participate in the study. Twenty-five of 106 doctors contacted in the North Rhine-Westphalia area of Germany agreed to participate in the study and to send us a list of all women of eligible age who had presented to their practice in the past two years. In Germany, women of this age group (48 to 49 years) contact their GP about four times a year on average [18].

To pseudonymize the women, all names are deleted from the list before it is sent to us, while the internal practice reference number remains for later identification. We then randomly select 24 women from each practice for inclusion in the study. Randomization is at patient level, that is, these 24 women are randomized per practice into two groups; A ('new brochure’) or B ('old brochure’). According to the random allocation, the women in groups A and B will receive the respective brochure, a letter, and a uniform questionnaire about knowledge and intention to take part in a screening. Closed envelopes which are marked only by the internal practice reference number are sent to the practices and from there directly to the women. With the attached letter they are asked to complete the questionnaire after reading the brochure and to send it back to us, without disclosing their identity, for pseudonymous analysis. The questionnaires contain a reference number that can only be decoded by the GPs.

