#### ***Questionnaire***

The questionnaire employed to elicit the women’s knowledge has been developed on the basis of already existing, partly validated questionnaires [12-15,17] and builds upon the criteria for relevant knowledge to make an informed decision [2] (Additional file 3). It contains five questions on *knowledge* (one point for every correct answer) [2,14]. Two questions measure *the women’s self-assessment of their knowledge* about mammography screening; two questions are about the perceived *relevance of knowledge* for the individual [12]. There is one yes/no question on the intention to participate (primary outcome), combined with a confidence rating for this decision (six-point scale from 'very unsure’ to 'absolutely sure’). Furthermore, there is one question each about personal experience with breast cancer, educational level, age, marital status and native language, two questions concerning the assessment of the brochure, and an open question for the participant to indicate information needs not sufficiently dealt with in the respective brochure. For secondary analyses we constructed items on the following topics: preferred media for support in screening decision, risk perception, attitudes towards mammography screening.

The questionnaire was pre-tested in 15 women with regard to comprehensibility, resulting in slight revisions of item wording and scaling.

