### Statistical analysis

The primary analysis will include all women who consented to study participation and gave information on her intention to participate in a potential mammography screening (full analysis set). It consists of a likelihood ratio chi-square test of the intention to screening participation with a two-sided alpha of 5%. As a sensitivity analysis, best and worst case analyses will be performed in all consenting women (intention-to-treat population) with different imputations for missing values. In a second step, a logistic regression model including potential confounders and effect modifiers (for example, knowledge) will be fitted to the data for further explanation of the primary result. Secondary endpoints (knowledge, self-assessed knowledge, importance of knowledge, confidence in decision) will be compared using chi-square tests or Mann–Whitney *U* tests, whichever appropriate.

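### The second-step logistic model names knowledge, an endpoint scored after the brochure is read, as a confounder or effect modifier, so its brochure coefficient is not the randomised effect

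*Protocol article*

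**What the plan says.** The Statistical analysis section of the protocol article makes the primary comparison an unadjusted likelihood ratio chi-square test of intention at a two-sided 5% level. It then adds a second step, in which "a logistic regression model including potential confounders and effect modifiers (for example, knowledge) will be fitted to the data"; the stated purpose is to explain the primary result. Knowledge is the only covariate named.

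The same section treats knowledge as an outcome: "Secondary endpoints (knowledge, self-assessed knowledge, importance of knowledge, confidence in decision) will be compared" between the arms. Under Research questions, the second question is "Do different information brochures lead to different knowledge about the potential benefits and harms of mammography screening".

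On timing, the Methods section says of the women that "they are asked to complete the questionnaire after reading the brochure and to send it back to us". According to the Questionnaire section, that one questionnaire contains both the five knowledge items, scored one point each, and the yes/no intention item. The article describes no measurement of knowledge before the brochure. Allocation is randomised at patient level within each practice.

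**The concern.** One variable is given two incompatible roles: a result of the brochure, and a factor to adjust for or stratify by when judging the brochure. Because allocation is random, knowledge cannot confound the brochure comparison. Because it is scored after the brochure, it cannot serve as a baseline effect modifier either.

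Conditioning on it has two consequences.

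- **The pathway is blocked.** Conveying facts is the main way in which the new brochure differs from the old. Any part of its effect on intention that runs through knowledge drops out of the adjusted coefficient.
- **Randomisation is broken within levels of knowledge.** A woman who scores 4 after the less informative brochure probably started with more interest or health literacy than a woman who scores 4 after the fuller one. If such traits also affect intention, the adjusted coefficient picks them up.

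At stake is the reading of the model. It is presented as explaining the primary result, so its brochure coefficient will be set beside the primary test. It could appear to contradict that test without the two estimating the same quantity.

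**Working it through.** **1. The plan's own figure.** The inputs, from the Sample size section, are 60% versus 45%, two-sided alpha 5% and power 80%. With pooled variance under the null and no continuity correction,

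n = [1.960·√(2·0.525·0.475) + 0.842·√(0.60·0.40 + 0.45·0.55)]² / 0.15² = (1.384 + 0.588)² / 0.0225 ≈ 172.8, so 173 per group.

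The other direction (60% versus 75%) gives 152, so 173 is the larger of the two. A noncentral chi-square calculation for the likelihood ratio test gives 173.3. At 50% response, 346 / 0.5 = 692. The stated figures reproduce, and none of them depends on the second-step model.

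**2. The role of knowledge, from the text.**

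- Affected by allocation? Expected: it is the subject of research question 2 and is compared between arms as an endpoint.
- Measured before allocation could act? No: the questionnaire is completed after reading.
- Able to influence intention? The plan supposes so, since it puts knowledge in a model for intention.

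These are the properties of a possible mediator. The conclusion needs no numbers.

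**3. Illustration of what conditioning can do.** The documents give neither a distribution of knowledge nor an association between knowledge and intention, so every parameter here is assumed.

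- Knowledge K is binomial with 5 items. Item logit = logit(0.45) + 1.0·A + a·U, where A = 1 for the new brochure and U is an unmeasured standard normal trait. Without U, mean K is 5·0.45 = 2.25 (old) and 5·0.69 = 3.45 (new).
- Intention Y has logit = logit(0.60) + b·(K − 2.25) + c·U, with no direct brochure term.
- Each setting has 173 per arm and 600 runs. The Monte Carlo standard error of a rejection rate is √(0.05·0.95/600) ≈ 0.9 points near 5%, and about 2 points near 48%.

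| Setting | Intention, old vs new | log-OR without K (rejection) | log-OR with K (rejection) |
|---|---|---|---|
| Full mediation, b = −0.4 | 60% vs 48% | −0.46 (56%) | 0.00 (5%) |
| Full mediation, b = −0.5 | 59% vs 45% | −0.56 (70%) | 0.02 (4%) |
| Full mediation, b = −0.6 | 59% vs 43% | −0.66 (84%) | 0.02 (5%) |
| No effect on intention, a = c = 0.8 | 59% vs 59% | −0.01 (4%) | −0.40 (36%) |
| No effect on intention, a = c = 1 | 58% vs 58% | 0.00 (5%) | −0.47 (48%) |
| No effect on intention, a = 1, c = −1 | 58% vs 58% | 0.01 (5%) | +0.47 (48%) |

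With 100,000 per arm, the b = −0.5 setting gives −0.57 without K and 0.00 with it. The a = c = 1 setting gives 0.00 (−0.005) and −0.47. The shift is therefore systematic and not a small-sample effect.

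The first three rows are not bias in themselves: the direct effect really is zero there, and the coefficient says so. They show that the coefficient answers a different question from the primary test. The last three rows are bias, because the brochure has no effect on intention by any route. All settings enter knowledge as a main effect; none models a brochure-by-knowledge interaction.

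**The case against.** The strongest reply is that no confirmatory result is at risk. The hypothesis is tested without adjustment, the regression comes second, and the article never calls its brochure coefficient the randomised effect or lets it overrule the primary test. The study also aims to understand how factual information acts on decisions, and comparing models with and without knowledge is a familiar, if crude, way to ask that. This stands as a limit on scope, and exploring knowledge is legitimate. It does not rescue the text, which labels the variable a confounder or effect modifier and says nothing of mediation or of the assumption that mediation requires.

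A second reply is that the parenthesis may attach to effect modifiers alone. That reading is possible. The problem remains, because strata of a score that the brochure has altered no longer compare randomised groups. The simulated figures do not quantify that version.

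A third is that covariate lists and the interpretation of secondary models are commonly left to the analysis plan. That is true of the full list, but the use of knowledge is stated in the article itself.

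A reader might infer three stronger things that the document does not support.

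- **That other post-brochure responses are also in the model.** The article says only "For secondary analyses we constructed items on the following topics: preferred media for support in screening decision, risk perception, attitudes towards mammography screening", and lists self-assessed knowledge and confidence as endpoints to be compared. None is named as a covariate.
- **That education is an unmeasured source of bias.** The questionnaire records it, so it can be adjusted for. Health literacy and prior interest are not described as measured.
- **That the distortion has a known size or sign.** Reversing one assumed sign turns −0.47 into +0.47.

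**Conclusion.** The point holds for the second-step model only. As written, the plan conditions on a post-randomisation variable that it also treats as an effect of the brochure. The resulting brochure coefficient, or contrast within knowledge strata, is not the randomised effect, and it can hide a real effect or produce one that does not exist.

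This conclusion rests on the document's own account of when knowledge is measured and what it is for. The size does not: rejection falling from about 70% to 4%, or rising from about 5% to 36–48%, illustrates assumed parameters and does not predict this trial.

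It would be wrong to conclude that the primary result is compromised. That test contains no covariates, and its alpha, power and 173 per group stand. The change should be made, because it decides whether the explanatory model can be interpreted, but it does not bear on the main conclusion.

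**What to change.** Reword the sentence on the second-step model along these lines: the logistic regression of intention will include allocation and factors that the brochure cannot alter, namely age, education, marital status, native language and personal experience with breast cancer; effect modification will be examined for these factors only. All five are already on the questionnaire. Although they are recorded after the brochure, allocation does not change them. The same model serves research question 3.

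Take knowledge out of that model, and do not add other responses that the brochure may influence, such as confidence, attitudes or risk perception.

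If the role of knowledge is of interest, report a separate exploratory mediation analysis with direct and indirect effects, adjusted for the same factors. State its assumption that no unmeasured common cause of knowledge and intention remains, and do not present the result as an adjusted brochure effect. The mediation analysis depends on that assumption just as the planned model does, which is why it should be labelled exploratory.

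Cost: one sentence of analysis wording and a little more analysis work. No new data and no change of sample size are needed. The knowledge result carries an exploratory label.

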### Limitations

A possible influence of differences in the formal design of the two brochures on the decision to take part in the screening program is not subject of our examination; however, the two brochures are formally quite similar.

## Trial status

We are currently recruiting participants.

## Abbreviations

GP: General practitioner; EBPI: Evidence based medicine; NNS: Number needed to screen; BSE: Breast self examination; DICS: Ductal carcinoma *in situ*.
